**I. Aims of the Study:**

The Global Early Adolescent Study (GEAS) is the first international study exploring how gender norms evolve over time and inform a spectrum of adolescent health outcomes, including sexual and mental health, through the adolescent years. The first phase, consisting of formative research and the face validity and pilot testing of instruments among early adolescents 10-14 years of age across 15 countries, is nearing completion. IRB oversight for all instrument development was provided for the first phase under IRB #00005684. The present research plan is in reference to the second, longitudinal phase of the GEAS. This phase, like the first, will be conducted in multiple international sites. However, because the longitudinal phase will likely be paired with different interventions or approaches in the partner sites, protocol details will vary and thus IRB approval will be sought for each site separately. The present application is for conducting Phase 2 of the Global Early Adolescent Study in Kinshasa, Democratic Republic of the Congo (DRC).

The objective of Phase 1 of the GEAS was to develop a theoretically derived, cross-culturally validated set of instruments appropriate for use with early adolescents in urban poor settings. With pilot testing data collection coming to a close, Phase 1 has resulted in a set of survey instruments that measure perceptions of gender norms, attitudes toward gender equitability, school retention, empowerment, healthy sexuality, physical and mental health, sexual health, exposure to gender-based violence, and other ecological factors influencing adolescent health such as family and peer relationships, parental connectedness, and neighborhood cohesion.

This longitudinal phase builds on the first by exploring how gender norms relate to health across the adolescent years, beginning with early adolescence. The GEAS in Kinshasa has two sets of objectives: 1) To explore how perceptions of gender norms evolve across adolescence, the factors influencing these changes, and how perceptions of gender norms predict a spectrum of adolescent outcomes, and 2) Assess the impact of a gender norms transformative intervention developed and implemented by Save the Children. The intervention, Growing Up GREAT (GUG), and evaluation components are part of a larger project, *Passages*, which is led by the Institute for Reproductive Health (IRH) at Georgetown University. Our research partner is the Kinshasa School of Public Health (KSPH), which will implement the GEAS study. The Kinshasa component of the project has both USAID and Gates Foundation support.

In both an intervention and control group 1,400 young people ages 10-14 will be followed over a period of 4 years, with one additional year of data analysis. To gauge effectiveness of the intervention, we will assess the following measurable primary and secondary study outcomes:

Primary outcomes:

- Doubling of contraception use among sexually active youth
- 10% decrease in reports of exposure to gender-based violence (GBV) compared with the previous 6 months

Secondary outcome:

- 20% shift toward more gender-equitable attitudes and beliefs

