**III. Study Design**

**Overview of study design and methods.** The GEAS in Kinshasa will involve a quasi-experimental longitudinal (pretest-midline-posttest) design to compare changes in perceptions of gender norms and subsequent effects on adolescent health outcomes between a group of early adolescents receiving Save the Children’s GUG intervention and a non-intervention control group. The control group is an essential feature of the study and will allow the exploration of developmental changes in adolescent health in the absence of an intervention during this critical period of human development.

The selection of intervention and control groups, which will include a sample of both in-school youth (ISY) and out-of-school youth (OOSY), will be based on geography, school selection (the ISY samples), and self-selection of adolescents participating in the intervention activities, described in detail in Section IV, “Participants” below. All participants will complete a baseline survey (before the intervention begins) and will be surveyed every 6 months over a period of 5 years. The survey will be divided into 2 segments, each collected 6 months apart in order to collect a complete wave of data every year. Additionally, this approach will minimize respondent burden and minimize loss to follow-up due to frequency of contact. Starting with the second wave, the survey instrument will be modified to include questions appropriate for older adolescents, and at that time a supplemental IRB application/amendment will be submitted. Following the same procedure as in the Phase 1 pilot, data collection will be conducted by trained interviewers using mobile tablets with the capacity for face-to-face interview also known as CAPI (computer-assisted personal interview), computer-assisted self-interview (CASI), and/or ACASI (audio computer-assisted self-interview) survey administration. When CAPI is the primary administration method, CASI/ACASI will be used for potentially uncomfortable questions, such as those about adverse childhood experiences and sexual and reproductive health, in order to increase privacy and improve data quality. We will continue to use the secure survey design and data collection software (SurveyCTO) used during the Phase 1 pilot test, which greatly improves data security over other methods.

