**Sample size and justification**

In each arm of the study 1,400 youth will be recruited for a total of 2,800 participants. The intervention arm will include 1,000 ISY and 400 OOSY, and the control arm will also include 1,000 ISY and 400 OOSY.

The sample size calculation is based on the frequency of intervention endpoints, the effect size of the intervention, the cluster design and related design effect, as well as expected cohort attrition rate all calculated in the school sample.

We assume a cluster size of 25, an intra-class correlation of 0.15 and 20% attrition per cluster.

The power calculation for contraception is calculated among the girl sample (cluster of 10 girls per school accounting for the 20% attrition). Baseline contraceptive prevalence in Kinshasa among 15-17 year old adolescents is 13%, based on recent PMA2020 data collected in 2016. A cluster sample of 500 adolescents per group (40 clusters) will detect a doubling of contraceptive prevalence in the intervention arm with a power of 79%. The pregnancy rate of 5% based on PMA2020 estimate is too low to be able to detect a difference between intervention and control groups in this study.

Calculations were done using the Stata clustersampsi command for the two primary outcomes:

- Contraception: clustersampsi, binomial samplesize p1(0.13) p2(0.26) k(80) rho(0.2) alpha(0.05) beta(0.8)
- GBV: clustersampsi, binomial samplesize p1(0.10) p2(0.05) k(40) rho(0.02) alpha(0.05) beta(0.8)

All other indicators including attitudinal and knowledge measures are based on continuous scores. Calculations based on preliminary results from the gender norms scales from the pilot GEAS in Kinshasa indicate that a sample size of 800 adolescents (40 clusters of 20 adolescents each, after attrition) is sufficient to detect a 10% shift in the gender scores between the intervention and control groups.

Table 3. Sample size calculation

| **Endpoints** | *Control* | ***Effect size*** | *Intra-class correlation* | ***Power*** | ***N clusters /arm*** | ***Minimum average students/ cluster*** | ***N participants / arm*** |
| --- | --- | --- | --- | --- | --- | --- | --- |
| **Attitudes** |  |  |  |  |  |  |  |
| Stereotypical gender norms (continuous score 13 to 62) | *Scale 1 Mean=3.99*  *SD=0.59*  *Scale 2*  *Mean=3.55*  *SD=0.69* | *Scale 1 detectable different =0.14*  *Scale 2 detectable different =0.17* | *0.15* | *80%* | *40* | *20* | *800* |

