Participants in the intervention arm will take part in an intervention program (GUG), which was found to produce positive outcomes in Uganda and Nepal and has been adapted for use in Kinshasa by Save the Children. Save the Children will hire and train staff from youth-centered CBOs to implement out-of-school components and will train teachers on how to use the in-school components. Parents of youth in the intervention arm will be invited to take part in one component. Participants will be engaged in the intervention will be in place for one school year.

Participants in both the intervention and control arms will take part in a baseline survey and will be surveyed again every 6 months over a period of 4 years.

Parents in both study arms will take part in a baseline questionnaire.

2. Describe the number and type of study visits and/or contacts between the study team and the participant, how long they will last, and where/how they will take place.

Follow-up surveys will be given every 6 months over a period of 4 years. While the baseline survey may take up to 1.5 hours to complete, follow-up surveys will last not more than 45 minutes. In-school adolescents will be surveyed at school or a nearby community center, and out-of-school adolescents will be surveyed at a local community center. The survey will primarily be interviewer-facilitated, but CASI/ACASI will be used for certain sections for increased privacy, as noted above.

All parents of participating youth will complete a short questionnaire with an interviewer at the time of consent; these interviews will be conducted in either French or Lingala as the participant prefers and last not more than 15 minutes.

Our partners at KSPH work closely with community liaisons who know participants, their families, and their locations. Parental contact information will be securely stored and used to contact parents of participants who have moved. If necessary and possible, the survey may be conducted by phone. Otherwise, the participant will be among those lost-to-follow up.

3. Describe the expected duration of the study from the perspective of the individual participant and duration overall.

Five years overall, with the participant involved for 4 years of data collection.

4. Provide a brief data analysis plan and a description of variables to be derived.

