1. Describe any potential direct benefits the study offers to participants (“payment” for participation is not a direct personal benefit).

Those in the intervention arm of the study will benefit from an evidence-based program that has been developed and implemented by Save the Children. Previous research suggests that the intervention is effective in increasing gender equitability and shifting gender norm attitudes that benefit participants. We hypothesize that those who will be participants will also be improved contraceptive users and less likely to be perpetrators or victims of gender-based violence.

There is no direct benefit to participants in the control group beyond what has been previously reported as the benefits research subjects feel in being able to share their experiences, exposures and perspectives.

Participants in both groups will be provided a meal and a t-shirt with the study logo.

1. Describe potential societal benefits likely to derive from the research, including value of knowledge learned.

The evidence is that gender-based violence is endemic in the DRC and the direct hypothesized benefit is that the intervention will reduce GBV by 20% and double effective contraception. Additionally, we hypothesize that there will be secondary benefits of more gender equitable relationships between boys and girls in the intervention group, improved mental health outcomes and an increase in healthy sexuality and school retention.

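### Contraception use is a primary outcome among sexually active youth, a denominator that probably forms largely after baseline, so a shift in sexual debut alone could move the result in either direction

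*Protocol*

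**What the plan says.** Section I (Aims) lists "Doubling of contraception use among sexually active youth" as the first of two primary outcomes. It also states that in each arm "1,400 young people ages 10-14 will be followed over a period of 4 years". Section III (Study Design) puts baseline ahead of the programme: "All participants will complete a baseline survey (before the intervention begins". It adds: "Starting with the second wave, the survey instrument will be modified to include questions appropriate for older adolescents". Section V.C (Study Implementation) gives the programme a length of one school year.

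The sample-size section takes its control rate from an older group: "Baseline contraceptive prevalence in Kinshasa among 15-17 year old adolescents is 13" per cent. It powers contraception on the girls in the school sample, with 10 per school after attrition in the text, and 11 per school or 440 girls per arm in Table 3. Neither place applies a restriction to sexually active girls.

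On the programme's reach, Section II (Background) says that gender norms have a substantial influence on sexual behaviour. The brief data analysis plan in Section V.C counts sexual behaviours among the main outcomes of interest. The text on societal benefits hypothesises "improved mental health outcomes and an increase in healthy sexuality and school retention".

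**The concern.** A between-arm comparison is like with like when the group compared is fixed before exposure. Here membership of the denominator depends on becoming sexually active. For children enrolled at 10-14, that will often happen during or after the programme year. If the programme changes who becomes active, or when, the sexually active youth in the two arms are differently selected groups. Adjusting for baseline cannot repair this, because a participant not yet active at baseline has no baseline contraceptive value.

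The risk is misreading. A higher proportion could reflect later debut among youth unlikely to use contraception. A real gain could be masked if the shift runs the other way. The problem lies in how the outcome is defined and would exist at any sample size, even with comparable arms.

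**Working it through.** **Timing.** Entry is at 10-14 and baseline comes before the programme. No participant is 15-17 at entry, yet the planning rate belongs to that age group. The protocol thus expects the outcome to arise during follow-up. It gives no share sexually active at baseline, so formation largely after baseline is an inference.

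**The plan's own figure.** The command uses "p1(0.13) p2(0.26) k(80) rho(0.2) alpha(0.05) beta(0.8". With 40 clusters per arm, m girls per cluster and ICC 0.2, effective n = 40m / [1 + (m − 1) × 0.2]. Power = Φ[(|p2 − p1| − 1.96·SE0) / SE1], with SE0 pooled and SE1 unpooled, two-sided 5%.

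- m = 10: 400 / 2.8 = 142.9 per arm, power 79.5%.
- m = 11: 440 / 3.0 = 146.7 per arm, power 80.6%.

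The stated 79% is reproduced, on 40 clusters per arm and on all girls retained. That is not the denominator in Section I, which is sexually active youth. The protocol does not say whether 13% refers to all 15-17-year-olds or to the sexually active among them. On either reading, the outcome and the calculation count different people.

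**Effect of a debut shift alone.** All inputs here are assumed, except the 13%, which is taken to apply to sexually active controls. Let 30% of controls be active, in two groups with 40% and 5% use. The high-use share p solves 0.40p + 0.05(1 − p) = 0.13, so p = 0.08 / 0.35 = 0.229.

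- High-use group: 0.30 × 0.229 = 0.0686 of all youth.
- Low-use group: 0.2314 of all youth.
- Users in controls: 0.40 × 0.0686 + 0.05 × 0.2314 = 0.0390.

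Now remove part of a group from the active through delayed debut, leaving use within each group unchanged. For one third of the low-use group:

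- Active: 0.0686 + 0.1543 = 0.2229.
- Users: 0.0274 + 0.0077 = 0.0351.
- Ratio of users to active: 0.158.

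The other rows follow the same way. All columns except the last two are percentages of all youth.

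| Scenario | Active | Active, using | Active, not using | Use among active | Ratio to control |
|---|---|---|---|---|---|
| Control | 30.0 | 3.9 | 26.1 | 13.0% | – |
| 1/3 of low-use group delayed | 22.3 | 3.5 | 18.8 | 15.8% | 1.21 |
| 1/2 of low-use group delayed | 18.4 | 3.3 | 15.1 | 18.0% | 1.39 |
| 1/3 of high-use group delayed | 27.7 | 3.0 | 24.7 | 10.8% | 0.83 |
| 1/2 of high-use group delayed | 26.6 | 2.5 | 24.0 | 9.5% | 0.73 |
| 1/3 of both groups delayed | 20.0 | 2.6 | 17.4 | 13.0% | 1.00 |

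The assumed 30% cancels from the ratio, so the share active does not drive the distortion. What drives it is how far the shifted youth differ in use from the rest.

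**Limits.** If a share s of would-be active youth is delayed and they would have used at rate d, use among the remainder is (0.13 − s·d) / (1 − s). At s = 0.5 this gives:

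- d = 0: 26%, the whole target effect.
- d = 0.05: 21%.
- d = 0.13: 13%, no bias.

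**The case against.** The strongest reply is that nothing in the protocol names sexual debut, delay or abstinence as a programme target. Healthy sexuality is left undefined, and the Background statement concerns gender norms in general. The bias needs two undocumented conditions: an effect on debut, and different contraceptive use among the youth whose debut shifts. The upward scenarios are also large, since they imply 26% or 39% fewer active youth (7.7/30 and 11.6/30) after a one-year programme. Even then the ratio stops at 1.39, short of a doubling. All of this stands, and it keeps the figures illustrative.

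It can also be said that contraceptive use has meaning only among the sexually active, and that reporting activity by arm is commonly left to a statistical analysis plan, which is not shown. The first is a good reason to keep the outcome. The second answers only part of the point, because the protocol itself fixes the denominator in Section I and uses another in the sample-size section.

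A reader might go further and infer that the primary outcome must be replaced by being sexually active and not using contraception, among all enrolled. The documents do not support that. The stated hypothesis concerns contraceptive use, and the composite itself falls from 26.1% to 18.8% or 15.1% in the table above through delayed debut alone. Choosing it would change the question and require a new control rate and power calculation.

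**Conclusion.** The concern holds in a limited form. The stated denominator probably forms largely after baseline and may be affected by the programme. The primary result can then move up or down with no change in contraceptive behaviour, provided that debut shifts and that the youth concerned differ in use from the rest. Under the assumed mix, the upward shift is from 13% to 15.8% or 18.0%, and the mirror case goes down to 10.8% or 9.5%. It is nil if the shifted youth would have used at 13%.

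A reader might infer that the programme will change debut, that any bias must favour it, or that the question cannot be answered. None of these follows from the documents. The outcome is interpretable when the share active in each arm is shown beside it. The mismatch between Section I (sexually active youth) and the sample-size section (all girls) is plain in the text and depends on no assumption.

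**What to change.** State one denominator for contraception in Section I and the sample-size section, or explain why they differ, and say to whom the 13% applies.

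Keep use among sexually active youth as stated. Add a pre-stated between-arm comparison among all enrolled youth (all enrolled girls for the Table 3 analysis) of status at the final survey: not sexually active; active and using contraception; active and not using. State that improved contraceptive use will be concluded only when the conditional result is read together with the proportion sexually active in each arm and the all-enrolled comparison. The composite need not replace the primary outcome.

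The cost is protocol wording, a little more analysis and a more guarded conclusion. No new participants or items are needed, because the outcome already requires asking about sexual activity and contraceptive use. The stated 79% power does not cover the all-enrolled comparison, and the protocol should say so.

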| Discussed contraception | *6%* | *RR=2.5* | *0.20* | *76%* | *40* | *20* | *800* |
| **Behavioral** |  |  |  |  |  |  |  |
| Proportion using modern contraception | *13%* | *RR=2* | *0.2* | *79%* | *40* | *11* | *440 girls* |
| Pregnancy | *5%* | *RR=0.5* |  | *27%* | *40* | *20* |  |
| Exposure to gender based violence in the last 6 Months (dichotomous) | *10%* | *RR=0.5* | *0.2* | *0.98* | *40* | *20* | *560* |

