Initially at baseline descriptive analyses will be done to test for comparability of intervention and comparison groups. Subsequently bivariate statistics (Chi-Square and Student’s t-test) will be run exploring the relationships between independent variables and key outcomes. Finally multivariate analyses will be performed to evaluate associations between gender norms, empowerment and the primary outcomes of interest sexual behaviors and outcomes, gender based violence and mental health. Over time, tests of differences will be run exploring change in gender equitable attitudes, gender norms and how these changes predict changes in prevalence of gender based violence and contraceptive utilization between intervention and control groups.

5. Describe whether you are collecting or storing personal identifiers, and if yes, why you need them, and when and how you plan to dispose of them. Signatures on consent forms are considered to be identifiers.

Participants will be assigned a unique identifier, which will be recorded with their responses during electronic data collection. A separate document containing participant’s photograph, identification number, name, age, and location will be kept in a locked file cabinet at KSPH for data collectors to contact participants for follow-up. These will be retained with consent and assent forms in a dedicated and locked cabinet that will only accessed by the site PI and the study coordinator. All electronic data will be encrypted. All documents with contact information will be destroyed immediately following the last wave of data collection and only coded data without any identifiers will be retained.

6. Answer the following **if they are relevant to your study design**

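### The primary GBV outcome is a 10% decrease on the previous 6 months, but the study is sized for a between-arm halving at an ICC the protocol states inconsistently

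*Protocol*

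**What the plan says.** The protocol gives the GBV effect in three places and its comparator in two forms.

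- **Section I, Aims.** Among the measurable outcomes for judging effectiveness, the second primary outcome is a "10% decrease in reports of exposure to gender-based violence (GBV) compared with the previous 6 months". No scale (relative or absolute) is given, and the line names no control arm.
- **Sample size and justification.** The Stata command takes 10% against 5% with 40 clusters ("GBV: clustersampsi, binomial samplesize p1(0.10) p2(0.05) k(40) rho(0.02) alpha(0.05) beta(0.8"). The GBV row of Table 3 repeats the 10% control rate as RR 0.5, but with an intra-class correlation (ICC) of 0.2, power 0.98, 40 clusters per arm, 20 students per cluster and 560 participants per arm. The general assumption above the commands is different again: "We assume a cluster size of 25, an intra-class correlation of 0.15 and 20% attrition per cluster".
- **Societal-benefits answer** (between Sections VII and IX). It hypothesises that "the intervention will reduce GBV by 20% and double effective contraception".
- **Comparator.** Section III describes a pretest-midline-posttest design with a control group that it calls essential. The data analysis plan (Section V, part C, item 4) tests "changes in prevalence of gender based violence and contraceptive utilization between intervention and control groups".

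**The concern.** A primary outcome that states a target should match the effect for which the study is sized. Here the target in the aims is one fifth of the relative effect in the sample size calculation. If 10% is the effect of interest, the study has almost no chance of showing it, and a null result would say nothing about it. If the halving is the effect of interest, the aims misstate the outcome.

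The comparator wording adds to this. Read literally, the line in Section I could be met by a fall over time in the intervention group without reference to controls. In participants who start at 10-14 and are followed for years, such a fall cannot be separated from developmental change, which is the reason Section III gives for having a control group.

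**Working it through.** **Inputs.** From the protocol: control rate 10%; 40 schools per arm; 25 students per school less 20% attrition, so 20 per school and 800 per arm; GBV ICC 0.02 (command) or 0.2 (Table 3); alpha 0.05. Assumed: a two-sided test, and beta(0.8) read as 80% power.

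**1. Reproducing the protocol's 560 per arm.** Without clustering,

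n = [1.960·√(2p̄q̄) + 0.842·√(p1q1 + p2q2)]² / (p1 − p2)².

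For 10% against 5%: (1.960 × 0.3725 + 0.842 × 0.3708)² / 0.05² = 434.4, so 435 per arm.

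With k clusters per arm the cluster size needed is m = n(1 − ICC)/(k − n·ICC).

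- ICC 0.02: 435 × 0.98 / (40 − 8.7) = 13.6, rounded up to 14, and 14 × 40 = 560. This matches Table 3.
- ICC 0.2: the denominator is 40 − 87 = −47, so no cluster size gives 80% power with 40 schools per arm.

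The 560 therefore belongs to a halving at ICC 0.02 and 80% power, not to the ICC of 0.2 or the power of 0.98 in the same row.

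**2. Power for each stated effect, 800 per arm.** Design effect = 1 + 19 × ICC, which is 1.38 at 0.02 and 4.8 at 0.2. The effective n is 800/1.38 = 579.7 or 800/4.8 = 166.7 per arm.

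Power = Φ{[|p1 − p2|·√n_eff − 1.960·√(2p̄q̄)] / √(p1q1 + p2q2)}.

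Example, 10% against 9% at ICC 0.02: (0.2408 − 0.8128)/0.4146 = −1.38, so power is 0.084.

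| Effect | ICC 0.02 | ICC 0.2 | Unclustered n per arm for 80% power |
|---|---|---|---|
| 10% to 9% (10% relative, Section I) | 0.084 | 0.050 | 13,495 |
| 10% to 8% (20% relative, benefits answer) | 0.220 | 0.093 | 3,213 |
| 10% to 5% (RR 0.5, sample size) | 0.899 | 0.410 | 435 |

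Multiplying the last column by the design effect at 20 per school, a 10% decrease needs about 18,600 per arm at ICC 0.02 and 64,800 at 0.2. A 20% decrease needs about 4,430 and 15,400.

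At the general ICC of 0.15, power for 10% against 5% is 0.49. The tabulated 0.98 is approached in the school sample only if clustering is ignored: 0.967 two-sided, 0.985 one-sided.

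**3. Absolute reading.** A fall of 10 percentage points from 10% is a fall to zero, twice the 5 points used for sizing.

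**4. Out-of-school youth.** These are left out above because the protocol says the calculation is for the school sample. Assume that 400 × 0.8 = 320 per arm remain, that they are unclustered and that they have the same rates. Adding them gives an effective n of 899.7 (ICC 0.02) or 486.7 (ICC 0.2). This is a best case. Power is then 0.08-0.11 for 10% to 9%, 0.19-0.32 for 10% to 8% and 0.84-0.98 for 10% to 5%.

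**5. Other control rates (an assumption; the protocol gives only 10%).** In the school sample with 20% to 50% in the control arm, power for a 10% relative decrease runs from about 7% (20%, ICC 0.2) to 40% (50%, ICC 0.02).

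**The case against.** The strongest reply is that the trial is clearly a between-arm comparison. Section III, the sample size commands, Table 3 and the analysis plan all say so. The Section I line follows directly on the naming of the two groups, and its 6-month phrase may be a garbled recall window, since Table 3 defines GBV exposure over the last 6 months. This stands. A reader might infer that the trial adopts an uncontrolled before-after analysis and so cannot attribute any change to the intervention. The documents do not support that: one line conflicts with a comparator fixed elsewhere. The line still defines a primary outcome and still needs correcting.

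The 20% is also not a success criterion. It answers an ethics-form question on societal benefit and is labelled a hypothesis. That stands too, but the conflict between 10% and RR 0.5 does not depend on it.

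A reader might go further from Section III, which says "The survey will be divided into 2 segments, each collected 6 months apart in order to collect a complete wave of data every year", and infer that no GBV value exists for the preceding 6 months or that half of each year goes unmeasured. The protocol does not say which segment carries the GBV items, and the instrument is an appendix not shown. A between-arm comparison needs no preceding 6-month value, and a 6-month prevalence measured once a year is a legitimate outcome. Nothing here supports asking the items more often.

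Finally, the out-of-school youth add information. They do not rescue the 10% target (at most about 11% power). On the optimistic assumptions above they do help the halving considerably, but the protocol does not claim them for its calculation.

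**Conclusion.** The point holds. The primary GBV target in Section I is not the effect for which the study is sized. On the protocol's own control rate and school sample, the chance of detecting it is about 5% to 8%, and for the 20% in the benefits answer about 9% to 22%. No reading of the 10% reconciles the passages: the relative reading is undetectable and the absolute one requires zero GBV. The comparator wording contradicts the rest of the protocol but is a drafting fault, not the adopted analysis.

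Moving everything to RR 0.5 is not enough by itself. In the school sample that effect has power of about 0.90 at ICC 0.02 and 0.41 at ICC 0.2, and the protocol gives both values for the same outcome.

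These figures rest on a two-sided 5% test, one follow-up cross-section, 20 students left per school and a 10% control rate. They take no credit for baseline adjustment, about which the protocol gives no correlation. A much higher control rate would make a 20% decrease more detectable (0.45 to 0.93 at a 50% control rate, over the two ICCs), but a 10% decrease would still reach no more than about 40% power.

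**What to change.** 1. **Section I.** Reword the GBV outcome as the proportion reporting any GBV in the last 6 months at a named wave, intervention against control, adjusted for baseline.
2. **One target effect.** Give a single effect, with its scale, in the aims, the commands, Table 3 and the benefits answer. The natural choice is the 10% against 5% used for sizing. If the 10% or 20% figures stay as aspirations, state that relative decreases of that size are not detectable at the assumed control rate.
3. **ICC and power.** Choose and justify one GBV ICC (0.02 in the command, 0.2 in Table 3, 0.15 in the general text), then restate power and participants per arm on that value, so that the 20 per cluster, 560 and 0.98 in the Table 3 row agree. If the ICC is near 0.2, say that the school sample gives only about 0.41 power for the halving. If the out-of-school youth are to count, state how and with what clustering.

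The cost is protocol wording and a short recalculation. There is no change to recruitment, survey content or visit schedule unless the settled ICC leads the investigators to reconsider the number of schools.
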